### Blinding

Due to the nature of the interventions, it is not possible to blind participants, but assessments/evaluation will be carried out in a blinded manner.

### Interventions

#### Standard care (SC) alone

The participant will receive the best SC provided by the local recruiting centre. On the day of surgery, excision of the KC is undertaken. The surgeon may perform partial closure (eg, purse string suture) and then the wound is dressed as per local practice. Immediate postoperative dressings may include haemostatic products such as alginate dressings. The patient is discharged with a standard information leaflet which includes contact phone details in case of concern about bleeding, infection or other AE.

Postoperative care and wound management will be provided according to local policies, typically seen twice weekly initially for 2–4 weeks in the SCSC. Subsequently visits reduce in frequency with either secondary care or primary or community care on a planned or ad hoc basis until healed. Additional advice regarding mobility/activity, emollient use and skin care may be provided by the attending clinical teams.

#### SC+CT

SC will be provided as previously described. In addition, CT will be initiated on the day of surgery in the SCSC and continued throughout the episode of wound treatment until healing. Trial CT will deliver pressures between 18–40 mm Hg at the ankle, that is, CT will comprise below-knee hosiery or bandage system.^18^ Bandages will be applied to the lower limb, excluding the toes and finishing below the knee. Hosiery must be a minimum of below-knee and may be open or closed toe. A list of approved compression therapies is available.

Compression choice (hosiery vs bandage system) will be based on patient preferences and clinician’s discretion from research-informed^13
14
18^ trial-approved product list; the rationale for choice will be reported, for example, ability to self-manage, compression-related discomfort, patient lifestyle, amount of oedema, pain, frequency of dressing changes, planned follow-up pathway. The underlying principle is the provision of compression until healing.

Where randomised to CT, compression will be applied as soon as possible, and additional information provided in respect of the CT. Frequency of hosiery change will be determined by ability to self-care and/or frequency of SC wound dressing changes. Frequency of bandage system changes will be determined by frequency of SC wound dressing changes.

### Assessments and data collection

Only data items that meet the study objectives have been included. PPIE involvement in the design of patient information and data collection forms and participant feedback has been incorporated to promote data completion and minimise missing data.

Baseline assessments and follow-up until confirmed healing (weekly up to 26 weeks then monthly where applicable, maximum 52 weeks) will be undertaken by a member of the clinical research team (eg, clinician, clinical research nurse or Registered Healthcare Professional (RHCP)). Follow-up phone calls may be completed by a non-RHCP, for example, clinical trials assistant.

Follow-up data collection will be via phone calls or can be face-to-face if attending the SCSC for routine clinic visits. If this is not possible, a member of the clinical research team may visit the patient in a community wounds clinic or at home. In-person visits are required at week four and confirmation of healing. Where an in-person visit with a member of the clinical research team is not possible, then a video call using NHS-approved technology with a photograph taken via screenshot can be submitted. In the unlikely event that neither an in-person visit nor a video call using NHS-approved technology can take place, then a photograph taken by the participant or participant’s associate can be submitted to the local research team who will then send by Secure File Transfer to CTRU.

Participants recruited more than 6 months before the end of the recruitment phase will be followed up to 4 weeks after confirmed healing, up to a maximum of 52 weeks (+7 days). Participants recruited during the final 6 months of the recruitment phase will be followed up to 4 weeks post confirmed healing for between 26 and 52 weeks (+7 days).

When the participant indicates their wound has healed at a follow-up visit or phone call, a confirmation of healing visit will be arranged. They will be asked to remove all dressings and stop using compression prior to the confirmation visit. A blinded assessor (healthcare professional) will assess and photograph the wound. If confirmed, a follow-up phone call will be completed 4 weeks after the healing confirmation visit (up to a maximum of 52 weeks post randomisation) to determine whether the wound has broken down.

If the wound is assessed as unhealed at the confirmation of healing visit, a photograph will be taken, and routine weekly/monthly phone calls and randomised treatment will be reinstated.

Medical record review will be undertaken at 26 and 52 weeks (where applicable, if not healed at 26 weeks) to capture related SAEs (including hospitalisations and related infections) and date patient last known to have an unhealed wound. Record review to also be performed on an ad-hoc basis if the participant dies, withdraws or is lost to follow-up.

The following information will be recorded:

#### Baseline assessment on the day of surgery/randomisation

Demographic information.Relevant medical history and clinical assessments.ABPI or Toe Pressure.CEAP.Factors affecting healing.Mobility.Questionnaire.EQ-5D-5L.In theatre.Post excision wound measurement – length, width, depth (excision to fat/excision to fascia or periosteum).Type of partial closure (purse string suture, side-to-side partial closure, eg, with pulley sutures or buried sutures, none).Post partial closure measurement (where applicable) – length and width.Following randomisationParticipant trial ID number.Randomisation allocation and details of intervention application.Date.Antibiotics.Related expected adverse and SAEs.

#### Follow-up phone calls/clinic visit

Wound status healed/unhealed.Antibiotic use.Any further surgery on the wound.Treatment application and adherence.Related expected/unexpected adverse and SAEs.

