#### Secondary objectives

To compare groups for:

Incidence of infection as measured by modified Bluebelle Wound Healing Questionnaire (WHQ)^20^ until healing.Numbers of days participants prescribed antibiotics until healing.Scar quality as measured by Patient and Observer Scar Assessment Scale (POSAS).^21^Safety events including related complications and hospitalisations until healing (maximum 52 weeks post randomisation).Cost-effectiveness via a within-trial analysis and decision analytic model (DAM) assessed from a payer perspective measuring patient health-related quality of life in terms of Quality Adjusted Life Years (QALYs) meeting updated Consolidated Health Economic Evaluation Reporting Standards (CHEERS) 2022 updated reporting guidance.^22^Resource use and health-related quality of life (HRQoL) as measured by EuroQol 5 Dimensions 5 Levels questionnaire (EQ-5D-5L) to 26 weeks post randomisation (52 weeks where applicable, for unhealed participants only).The relationship between post-partial closure wound area, type of partial closure method, and time to healing.

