#### Week 4 clinic visit*

Wound assessment healed/unhealed.Wound measurement.Antibiotic use.Any further surgery on the wound.Treatment application and adherence.Photography.Related expected adverse and SAEs.Questionnaires.Modified Bluebelle WHQ.EQ-5D-5L.Health Resource Use.Intervention acceptability (CT only).

*If the week 4 clinic visit does not take place, a follow-up phone call will be made and questionnaires will be completed remotely.

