### Economic evaluation

The economic evaluation will assess the cost-utility of SC+CT compared to SC alone using within-trial analysis and a DAM to assess the argument over a longer time perspective. The proposed methods for the economic evaluation will follow the reference case set out by NICE.^39^

The within-trial analysis will be undertaken to estimate the resource use, costs and effects for both comparator arms for the 26-week follow-up period. The DAM will be developed over the course of the project, extrapolating to 52 weeks to help in assessing alignment with and validation by the within-trial analysis and providing some insight on cost-effectiveness drivers. The DAM will be based on a Markov model with states based on healed, unhealed, infected and dead. An NHS and Personal Social Services perspective for costs will be adopted.

Health resource use data will be collected from a questionnaire (see Data Collection and Questionnaire section) and from trial case report forms (CRFs). The information will include primary, secondary and community resource use. Unit cost data will be obtained from national databases such as the *National Schedule of Costs* (NHS England), the *Personal Social Services Research Unit (PSSRU) Costs of Health and Social Care* and the *British National Formulary (BNF*). All resource use will be valued in monetary terms using appropriate UK unit costs with the price year for which all costs can be valued and required adjustments made for inflation using the Office of National Statistics (ONS) Gross Domestic Product (GDP) deflator index.

Treatment costs include the costs of CT and of SC post-op care and wound management (clinic visits, dressings provided, staff time). Participants’ responses to the EQ-5D-5L questionnaire will be converted to utility scores using the newly published UK value set for the 5L version.^40^

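### Adverse events are collected only if they count as related, by staff who also record treatment use, so the between-group safety summary, including hospitalisations, can be distorted in either direction

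*Protocol article*

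**What the plan says.** *Secondary objectives* in the protocol article lists, among the outcomes on which the groups are compared, "Safety events including related complications and hospitalisations until healing (maximum 52 weeks post randomisation"). *Analysis of secondary outcome measures* says that these events will be summarised descriptively by the treatment received.

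The data collection sections give the content of each contact:

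- On the day of surgery, after randomisation: "Related expected adverse and SAEs". The week 4 clinic visit uses the same words.
- At follow-up calls and clinic visits: "Related expected/unexpected adverse and SAEs".
- The week-26 and week-52 record reviews list SAEs that are both related and expected. *Assessments and data collection* gives the purpose of these reviews as "to capture related SAEs (including hospitalisations and related infections"). The week-52 review covers only participants unhealed at week 26.

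On blinding, the article says that "it is not possible to blind participants" and adds a general statement that assessment will be blinded. A blinded assessor is specified only for the healing confirmation visit. On staffing, it says: "Follow-up phone calls may be completed by a non-RHCP, for example, clinical trials assistant".

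**The concern.** Relatedness works here as a condition for recording an event, not as an attribute of an event already recorded. At calls and at week 4 the condition is applied by people who, at the same contact, ask about use of the allocated treatment. Leg pain, skin damage or an admission may be classed differently according to whether the participant wears compression.

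The safety summary is where a reader will look for harm from compression. Differential classification could show an excess that is not there or hide one that is. Events left out at collection leave no trace in the adverse event data. That matters most for hospitalisations, which the objective names explicitly.

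**Working it through.** **1. The collection points side by side (all from the protocol article).**

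| Point | Must be related? | Other limits | Participants |
|---|---|---|---|
| Baseline, after randomisation | Yes | Expected only | All |
| Calls and clinic visits | Yes | Expected or unexpected | In follow-up |
| Week 4 visit | Yes | Expected only | All |
| Week-26 record review | Yes | Expected SAEs | All |
| Week-52 record review | Yes | Expected SAEs | Unhealed at week 26 |
| Ad hoc review on death, withdrawal or loss | Not stated | Content not listed | As triggered |

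The relatedness condition appears at every point that lists adverse events. (The table also shows that only the calls and visits admit unexpected events. That is a separate discrepancy, and those sections should be reconciled.)

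**2. Do the collectors know the arm?** *Follow-up phone calls/clinic visit* and *Week 4 clinic visit* both list treatment application and adherence with the safety item, and week 4 adds an acceptability questionnaire for the compression arm only. The general blinding statement therefore cannot describe these contacts.

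**3. What is collected without the condition?** Antibiotic use, further surgery on the wound, the wound healing questionnaire, healing status and the wound breakdown check carry no such limit. Resource use comes from questionnaires and from trial CRFs. The safety analysis text does not name resource use as a source for hospitalisations.

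**4. Deaths.** A death triggers an ad hoc record review, and the sensitivity analyses treat death as a possible competing risk, in neither case with a relatedness condition. Vital status is not among the items listed for the week-26 or week-52 review.

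**5. Possible size.** The plan gives no figure to reproduce on this point, and the sample size is unaffected. If the true risk is p in both arms, and fractions r0 (SC) and r1 (SC+CT) of events are classed as related, then

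- recorded count per arm = 198 × p × r
- apparent risk ratio = r1 / r0, whatever the value of p

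Inputs: 198 per group (*Sample size*); p = 3/53 = 5.7%, the feasibility cohort's hospitalisation for infection or cellulitis (*Patient burden*), which is the only hospitalisation rate given and is not all-cause. The fractions are assumptions. Expected true events per arm: 198 × 3/53 = 11.2.

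| r0 (SC) | r1 (SC+CT) | SC count | SC+CT count | Apparent RR | Difference (percentage points) |
|---|---|---|---|---|---|
| 1.0 | 1.0 | 11.2 | 11.2 | 1.00 | 0.0 |
| 0.9 | 0.7 | 10.1 | 7.8 | 0.78 | −1.1 |
| 0.7 | 0.9 | 7.8 | 10.1 | 1.29 | +1.1 |
| 0.9 | 0.5 | 10.1 | 5.6 | 0.56 | −2.3 |
| 0.5 | 0.9 | 5.6 | 10.1 | 1.80 | +2.3 |

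With equal fractions the ratio is undistorted. With unequal fractions it moves either way.

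**The case against.** The strongest reply is that limiting capture to related events can be defended in a pragmatic trial of an established therapy; the introduction cites venous ulcer evidence of no impact on adverse events. The safety analysis is descriptive, with no test. Infection, the main morbidity in the feasibility cohort, is measured by its own questionnaire. Who judges relatedness, and to what (surgery, wound or compression), is detail that an article commonly leaves to the full protocol. If it means related to surgery or the wound, both arms have something to which an event can be attributed.

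Much of this stands. It rules out four stronger readings that a reader might infer:

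- *That unblinded staff, perhaps a non-registered caller, make the causality judgement.* The article says only that such a person may complete calls. It names nobody as assessor.
- *That deaths are filtered by relatedness.* The text sets no such condition. The week-26 review also opens the records of healed participants, although it does not list vital status.
- *That the bias will run against compression.* The documents support neither a direction nor a size.
- *That admissions outside the condition are lost for good or exist only as patient recall.* Admissions can be looked up in medical records, and resource use also draws on CRFs.

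What the reply does not remove is the condition itself. A descriptive count is distorted by differential recording just as a tested one is. The wording of the objective may allow for events beyond related ones, but no safety list collects any. The one cited comparison in this surgical setting does not settle the matter: OR 0.67 with p = 0.74, if from a Wald test, gives z = 0.332, SE = 0.400/0.332 = 1.207 and a 95% CI of about 0.06 to 7.1.

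**Conclusion.** The point holds as a risk to the safety summary, not as a demonstrated bias. As written, all listed adverse event capture depends on relatedness, and at calls and week 4 the collectors also record treatment use. The between-group summary, including hospitalisations, can therefore be distorted in either direction.

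The size cannot be estimated from the documents. The range of 0.56 to 1.80 for the apparent risk ratio rests on assumed classification fractions and shows only what unequal classification could do; with equal classification the ratio is 1.00. The primary outcome and the sample size are not affected. The conclusion assumes that the lists in the article match the forms in use. If the full protocol records all admissions elsewhere for the safety analysis, the concern about hospitalisations falls away.

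**What to change.** Use the record reviews that are already scheduled:

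1. At the week-26 review (all participants) and the week-52 review (those unhealed at week 26), record every hospital admission with date and main cause, plus vital status and date of death, without a relatedness condition.
2. Complete these items from records for participants already past those reviews.
3. Keep relatedness as a field assigned after the event is recorded.
4. Report all-cause admissions and deaths by randomised arm, beside the planned summary of related events by treatment received. Weeks 0 to 26 give the cleaner comparison, because only unhealed participants have the later review. The dates also allow a count up to healing, as the objective specifies.

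The cost is a small CRF and protocol amendment, more entries per participant and some retrospective look-up. No new visits or staff are needed.

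Capturing every fall and every event on the index leg would go further, but it is a debatable trade-off at this stage. With 276 of 396 participants randomised by 31 December 2025, it would create two ascertainment regimes, and many past minor events would not be found in records.

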#### Week 4 clinic visit*

Wound assessment healed/unhealed.Wound measurement.Antibiotic use.Any further surgery on the wound.Treatment application and adherence.Photography.Related expected adverse and SAEs.Questionnaires.Modified Bluebelle WHQ.EQ-5D-5L.Health Resource Use.Intervention acceptability (CT only).

*If the week 4 clinic visit does not take place, a follow-up phone call will be made and questionnaires will be completed remotely.

#### Week 12 postal/electronic data collection

Questionnaires.Modified Bluebelle WHQ (if unhealed).EQ-5D-5L.Health Resource Use.

#### Week 26 postal/electronic data collection and record review

Postal/electronic questionnaires.Modified Bluebelle WHQ (if unhealed).EQ-5D-5L.Health Resource Use.Record review: a member of the research team will complete a review of the participant medical records and record the following information:Related and expected SAEs.Date wound last known to be unhealed (if applicable).Histology results/diagnosis.

#### Week 52 record review (if wound not healed at week 26)

A member of the research team will complete a review of the participant medical records and record the following information *only for participants whose wounds had not healed by Week 26*:Related and expected SAEs.Date wound last known to be unhealed (if applicable).Histology results/diagnosis.

#### Week 52 postal/electronic data collection (if wound not healed at week 52)

Postal/electronic questionnaires.Modified Bluebelle WHQ.EQ-5D-5L.Health Resource Use.

An ad hoc record review will be carried out if patient dies, withdraws or is lost to follow-up.

### Assessment of healing

Healing is defined as complete epithelial cover in the absence of a scab, eschar or crust (adapted from Chetter *et al*^20^ and Arundel *et al*^24^). Where participants indicate their wound has healed during a follow-up phone call, a confirmation of healing visit will be arranged within 7 days.

### Questionnaires

Participants must provide consent to complete questionnaires at the point of joining the study but may decline to complete a questionnaire at any time during follow-up and remain in the study. Baseline, week 4 and blinded healing assessment visit questionnaires will be administered in clinic on paper/verbally. If the participant does not attend the in-person week 4 clinic visit then questionnaires can be administered over the phone. Participants can choose their preferred method to receive other follow-up questionnaires (electronic/paper). Participants will receive 1 reminder message via their preferred method if a completed questionnaire has not been received within the expected time frame (2 weeks for return by post and 1 week for electronic submissions). The following questionnaires will be administered during the study:

Modified Bluebelle WHQ.POSAS.Intervention acceptability (CT only).EQ-5D-5L.Healthcare Resource Use.

#### Modified bluebelle wound healing questionnaire (WHQ)

The modified Bluebelle WHQ^20^ has been adapted from the original Bluebelle WHQ^25^ for relevance for patients with open wounds by removing three items relating to spontaneous or deliberate wound dehiscence and use of dressings given these would not be relevant in this population. The time frame for the questionnaire has also been adapted to indicate that the questionnaire should be completed since the participant had their open wound (at wound healing or since the last modified Bluebelle questionnaire was completed – weeks 4, 12, 26 and 52 weeks (where applicable, if wound is not healed)) post randomisation and at healing, where applicable rather than the time since hospital discharge.

#### Patient and observer scar assessment scale (POSAS)

The POSAS^21^ measures scar quality by evaluating visual, tactile and sensory characteristics of the scar from the perspective of the observer and patients.

#### Intervention acceptability

Intervention acceptability will be explored through questions developed with PPI input to consider comfort, convenience and appearance. Details will be completed by participants in the intervention arm at week 4 and at the confirmation of healing visit.

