### Primary objective

To compare the time to HBSI from randomisation, between SC and SC+CT.

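### A compression-only acceptability form is scheduled at the blinded confirmation-of-healing visit, giving the primary-endpoint assessor an avoidable way to learn the arm

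*Protocol article*

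**What the plan says.** All references are to the protocol article.

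- **Blinding.** Participants know their arm; the safeguard is that "assessments/evaluation will be carried out in a blinded manner". The abstract and the opening of Methods both present blinded endpoint assessment as a design feature.
- **Assessments and data collection.** When a participant reports healing, a confirmation visit is arranged. Before it, "They will be asked to remove all dressings and stop using compression prior to the confirmation visit". At it, "A blinded assessor (healthcare professional) will assess and photograph the wound". If the wound is judged unhealed, a photograph is taken, and the routine calls and randomised treatment resume.
- **Questionnaires.** The list includes "Intervention acceptability (CT only)". On delivery: "Baseline, week 4 and blinded healing assessment visit questionnaires will be administered in clinic on paper/verbally".
- **Intervention acceptability.** "Details will be completed by participants in the intervention arm at week 4 and at the confirmation of healing visit". The questions cover comfort, convenience and appearance.
- **Primary objective.** "To compare the time to HBSI from randomisation, between SC and SC+CT". The date of this event depends on the assessor's decision.
- **Oversight/trial monitoring group.** Endpoint validation and central review of photographs are among the group's duties.

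**The concern.** A questionnaire that exists in one arm only identifies the arm to anyone who sees whether it is in use. The article puts such a form, by name, at the visit that it calls blinded. The participant has been asked to arrive with compression off, so that the leg itself does not give the arm away. A compression questionnaire in the visit pack, or read aloud, can undo that step, and reading it aloud invites the participant to talk about compression.

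Healing is defined as full epithelial cover with no scab, eschar or crust. That is a visual call, and on a borderline wound it can go either way. An unhealed verdict sends the participant back into follow-up, so the recorded event date moves. If an assessor who knew the arm were slightly readier to confirm healing under compression, the hazard ratio would be biased in favour of SC+CT. Adjusting for wound area and depth would not remove that bias. The direction depends on what assessors expect, which the article cannot tell us.

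**Working it through.** **1. The passages side by side**

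| Question | What the article gives |
|---|---|
| Who gets the form? | Compression arm only |
| When? | Week 4 and the confirmation-of-healing visit |
| How, at that visit? | In clinic, on paper or verbally |
| Who decides healing there? | A blinded healthcare professional |
| Masking step described | Dressings and compression off beforehand |
| Who hands out or collects the form? | Not stated |
| Before or after the verdict? | Not stated |

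The first four rows are positive statements, and together they place an arm-identifying document at the blinded visit. The described masking step covers the leg, not the paperwork. The last two rows leave the risk open but do not show that it materialises.

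**2. The design scale**

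The sample size section gives a control median of 81 days, a target of 57 days (HR 1.43), two-sided 5%, 90% power, 10% attrition and 396 randomised. By Schoenfeld's formula:

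- events = 4(1.960 + 1.282)² / (ln 1.43)² = 42.03 / 0.1279 ≈ 329
- average probability of healing by 52 weeks, exponential with medians 81 and 57 days: (0.956 + 0.988)/2 = 0.972
- N = (329/0.972)/0.9 ≈ 377
- with 396 randomised: 396 × 0.9 × 0.972 ≈ 346 events, power about 0.91

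The stated figures reproduce and are unaffected by this point. HR 1.43 is used below only as a yardstick.

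**3. Choosing a healing curve**

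The article gives no curve, so I take a Weibull with median 81 days: proportion unhealed at day t = 0.5^((t/81)^k). The feasibility cohort had 4/53 = 7.5% known unhealed at 6 months and another 4/53 of unknown status, so 7.5% to 15.1%. At t = 182 days:

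| Shape k | Unhealed at 6 months |
|---|---|
| 1 (exponential) | 21% |
| 1.2 | 16% |
| 1.6 | 8.0% |
| 3 | 0.04% |

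A shape near 1.6 fits the known count. If the unknowns were all unhealed, the shape would be nearer 1.2. Shape 3 is not compatible with the cohort.

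**4. Illustrative bias**

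Simulation with no true effect: 356 analysed (396 less 10%), median 81 days in both arms, 7 days added to the healing time of a random fraction of SC participants, censoring at 364 days, unadjusted Cox model, 4,000 runs per setting.

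| Shape | 30% deferred: HR | 50% deferred: HR | 50% deferred: two-sided error |
|---|---|---|---|
| 1 | 1.02 | 1.03 | about 6% |
| 1.6 | 1.03 | 1.05 | about 8% |
| 3 | 1.07 | 1.11 | about 17% |

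At shape 1.6 with 30% deferred, the error is about 6%. On the log scale, ln 1.03/ln 1.43 = 0.030/0.358 ≈ 8% and ln 1.05/ln 1.43 = 0.049/0.358 ≈ 14% of the target effect. The 7-day step matches the weekly contact schedule. The 30% and 50% fractions are assumptions with no source in the article.

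**The case against.** The strongest reply is that this is a condensed article. Who hands over a form, and at what point in a visit, is operational detail that may well sit in the full protocol, which is not shown here. The acceptability section says that participants complete the form, and the blinded assessor is described separately from the research team who do baseline and follow-up. A site might naturally give the form only once healing is confirmed, or through another member of staff. This stands to the extent that a reader who infers that the blinding has failed goes beyond the text. It does not dispose of the point, because what the article does state is the schedule itself, and that schedule works against the blinding it claims.

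Second, other safeguards exist. Photographs are taken whether or not the wound is judged healed, and central review is listed, so it would be wrong to infer that the on-site assessor is the only protection. The mitigation is uncertain, because the article does not say that the review is blinded or decides the endpoint.

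Third, participants know their arm and may disclose it anyway. That is true, and the form's own contribution cannot be isolated. Chance remarks are hard to prevent, however, whereas a scheduled form is easy to move.

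Fourth, a reader might extend the point to the observer part of POSAS. The article names neither rater nor visit for it. POSAS is absent from the baseline and the week 4, 12, 26 and 52 lists, which makes the healing visit likely, but that remains an inference.

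**Conclusion.** The point holds as an avoidable and systematic risk of unblinding at the visit that fixes the primary endpoint. It is not a demonstrated breach. The form is scheduled for up to 198 SC+CT participants, and its absence could be equally informative for the 198 in SC.

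The probable bias is small: a null hazard ratio moving to about 1.03 to 1.05, with two-sided error of roughly 6% to 8%. This rests on a Weibull shape of about 1.6, one 7-day deferral confined to SC, and assumed deferral rates of 30% to 50%. If assessors do not see the form, or do not act on it, the bias through this route is nil. A reader could obtain a hazard ratio of about 1.11 and an error near 17% from a steeper curve (shape 3), but that curve leaves almost nobody unhealed at 6 months and contradicts the feasibility data.

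The reason to act is that the route is built into the schedule, the trial's credibility rests on blinded assessment, and the remedy costs almost nothing.

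**What to change.** Take the compression-only form out of the blinded visit, in either of two ways:

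- send it by the participant's preferred postal or electronic route once healing is confirmed; or
- collect it at the phone call already planned 4 weeks after confirmation. That call is capped at 52 weeks after randomisation, so a participant confirmed after about week 48 (52 − 4) may have none, and follow-up can end sooner for those recruited in the last 6 months. Use the postal/electronic route wherever there is no call.

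If the form must stay on the day, state that someone other than the assessor gives it, and only after the healing verdict, the photograph and any observer POSAS have been recorded. If the full protocol already says this, a sentence in the article settles the point. It would also help to record at each confirmation visit whether the assessor had learnt the arm.

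The cost is a short amendment to the protocol and visit instructions, recall up to about 4 weeks later, and a few unreturned forms. Acceptability is exploratory and summarised descriptively, so the loss is minor. Sample size and analysis are unchanged. With 276 of 396 randomised by 31 December 2025, at least the remaining 120 participants, and those still unhealed, could benefit.
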